### Study End Points

#### Primary End Points

The primary objective of the study is to compare changes in MGI by Lobene et al [29] between baseline and end of the study (ie, 18 months’ time point) among participants who continue to smoke tobacco cigarettes (arm A) and participants who switch to C-F NA (arm B).

#### Secondary End Points

In addition, the study will analyze the number of secondary objectives, including within- and between-group variations at each study time point from baseline for MGI assessment, plaque imaging, dental shade quantitation, tooth stain scores, and oral health–related quality of life questionnaires.

### Study Measurements and Calibration

A detailed description of the study measurements that will be specifically carried out at the dental clinic is provided in Multimedia Appendix 2.

All assessors will be trained on MGI scoring, tooth stain assessment, and the correct use of technologies and software used to quantify dental plaque, tooth discoloration, exhaled carbon monoxide monitoring, and electronic case report form (eCRF) use. Assessors will be periodically calibrated on MGI scoring and tooth stain assessment. To ensure consistency in the measurements, the same assessor will collect all study end points in the same participant over the entire study period.

### Data Monitoring and Study Safety

A trial monitoring plan will be developed based on the trial risk assessment and includes on-site monitoring. The clinical research organization will arrange an independent monitor, separate from the investigators and the sponsor, to ensure compliance with trial protocols and policies, participant protection, and accurate data collection.

AEs and serious AEs (SAEs; eg, those related to oral conditions, tobacco cigarette smoking, C-F NA use, nicotine withdrawal symptoms, or nicotine overdosing) will be recorded on the AE page of the eCRF throughout the study. Participants will be interviewed at each visit to investigate signs or symptoms. Signs or symptoms will be elicited at each visit by open questioning, such as “How have you been feeling since your last visit?” “How have you been feeling regarding your oral cavity?” Participants will also be encouraged to spontaneously report AEs occurring at any other time during the study via the dedicated mobile app or the communication channels provided for the study. The investigator must gather sufficient information to determine the outcome and causality of AEs and SAEs and promptly notify the competent authority, if necessary.

### Study Withdrawal

Participants may be withdrawn from the study prematurely for the following reasons: (1) experience an SAE, (2) develop a concurrent disease which at the discretion of the investigator no longer justifies the participant’s participation in this study, (3) sustain any uncorrectable protocol deviations during the study, (4) decide to stop their participation, (5) become pregnant, and (6) exhibit uncooperative behavior or nonattendance. After consultation with the clinical research organization, the investigator will notify participants’ discontinuation from the study.

### Data Collection and Protection

For data collection, each participant will be allocated an eCRF. Anonymized data from each study visit will be entered directly into the eCRF, which will then serve as a source document for the trial. This data entry process ensures that data are collected accurately and consistently at all study sites.

Each participant will be assigned a unique study identification number (participant ID). Participant’s personal data will not be linked to the research results, and only a limited number of members of the research team will have access to the decoding list that links participant IDs to their personal information. All information obtained during the study procedures, including participant data and personal details, will be treated as private and confidential in accordance with ethical and privacy regulations.

The trial will reach its formal conclusion on the date of the final visit of the last participant in the last country involved in the study.

### Ethical Considerations

The study will be conducted in accordance with the Principles of Good Clinical Practice and the Declaration of Helsinki. All 4 local ethics review boards reviewed and approved the study and, where appropriate, translated the relevant documentation (eg, informed consent form, participant’s information sheet). The trial is registered with ClinicalTrials.gov (NCT04649645). The study was approved by the ethics review board of the coordinating center, the Azienda Ospedaliera di Rilievo Nazionale e di Alta Specializzazione “Garibaldi” (697/CE; dated November 11, 2020). Informed consent was obtained from all the participants.

The intention is to disseminate the study results through articles in peer-reviewed journals and conference presentations. A summary of the results will be available on the study website for public access. The anonymized data will be available to researchers upon reasonable request.

### Statistical Considerations

#### Sample Size Calculation

For a valid sample size calculation, literature research was performed for the primary end point of the study (ie, MGI). Unfortunately, no data were available for such a study. However, data from studies with mouth rinse were available, and based on these studies [30,31], a mean MGI change of 0.08 with an SD of 0.18 of the MGI seemed relevant.

However, in these studies, higher mean MGI changes were observed because active treatment was administered, which was not the case in this study. Thus, several scenarios with different mean MGI changes and SDs will be applied.

The following hypotheses will be tested with a 1-sided independent *t* test:

H0: µA≤µB versus H1: µA>µB

where µA denotes the mean change MGI from baseline to after 18 months of regular smoking and µB denotes the mean MGI from baseline to after 18 months of C-F NA use.

For sample size calculation, SAS software (version 9.4; SAS Institute) was used and several scenarios were applied, assuming that the data are normally distributed. The results are summarized in Table 5, which presents the calculated sample sizes for the comparison of µA versus µB by a 1-sided independent *t* test, a significance level of 5%, and a power of 90%, depending on the expected MGI change and SD.

As no active treatment is given in this study, a lower effect than the observed values needs to be assumed. Therefore, a mean MGI change of 0.1 with an SD of 0.21 was chosen. Hence, a sample size of 77 patients per treatment group is required. Considering a dropout rate of 20% over 2 years’ observation phase [32,33], a sample size of at least 92 per treatment group is required. In addition, it is estimated that approximately 25% of those switching to C-F NA use will abstain or substantially (≥90%) reduce smoking [34], and only these participants deliver valid results. Therefore, 4 times more participants should be recruited in the C-F NA group (4 × 92 = 368). This results in a total sample size of 460 (92 in arm A+368 in arm B).

In arm C, we have determined a sample size of 40, empirically with no formal statistical analysis, as this cohort’s primary study end point (ie, MGI) is expected to be stable throughout the study.

**Table 5 table5:** Summary table including the sample size for each arm of the study depending on the mean Modified Gingival Index (MGI) change and SD.

Nominal power	Mean MGI change	SD^a^				
		0.20	0.21	0.22	0.23	0.24
0.9	0.10	70	77	84	92	100
0.9	0.15	32	35	38	41	45
0.9	0.20	18	20	22	24	26

^a^Expected sample size is the same per each group and it is indicated by the rows (ie, 70-100, 32-45, and 18-26) according to the SD and MGI combinations.

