**Methods:**

Regular smokers not intending to quit and without clinical signs of periodontitis will be randomly assigned (1:4 ratio) to either standard of care with brief cessation advice (control group; arm A) or C-F NA use (intervention group; arm B). The study will also include a reference group of never smokers (reference group; arm C). The primary end point is the change in the Modified Gingival Index (MGI) score from baseline between the control arm (arm A) and the intervention arm (arm B) at the 18-month follow-up. In addition, the study will analyze the within- and between-group (arms A, B, and C) changes in MGI assessment, plaque imaging, dental shade quantitation, tooth stain scores, and oral health–related quality of life questionnaires measured at each study time point. All participants will attend a total of 7 clinic visits: screening, enrollment, and randomization (visit 0); baseline visit—day 14 (visit 1); day 90 (visit 2); day 180 (visit 3); day 360 (visit 4); and day 540 (visit 5). This multicenter study will be conducted in 4 dental clinics in 4 countries. The statistical analysis will involve descriptive statistics for continuous and categorical data. Primary end points will undergo tests for normality and, based on distribution, either a 2-sided *t* test or Mann-Whitney *U* test. Linear mixed model with random factors center and study arms by center will also be applied. Secondary end points, including MGI assessment and quality of life, will be subjected to similar tests and comparisons. Only if one value of the parameter MGI is missing after day 1, the last available observation will be carried forward. The analysis will be performed on the substituted data. Secondary parameters will not have missing value replacement.

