**Conclusions:**

This will be the first study to provide key insights into oral health benefits or risks associated with using C-F NA in smokers who are seeking alternatives to cigarette smoking.

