#### Statistical Analyses

Statistical methods used in the analysis of this study will include descriptive statistics with the descriptive presentation of the total sample value, mean, SD, median, minimum, maximum, and 95% CIs for (pseudo) continuous data and categorical data. Further evaluations will be summarized in tables by counts and percentage of scores.

Statistical methods for primary study end points will include the following: the Shapiro-Wilk test of normality on calculated values (in case of normal distribution, a 2-sided independent *t* test and in case of nonnormal distribution: a 2-sided Mann-Whitney *U* test) and a linear mixed model with the random factors “center” and “study arms by center.”

Designated as study arm C, the never-smoker group will establish a baseline reference for the oral health parameters. This group is anticipated to provide insights into the underlying changes in the primary study end point (MGI) that may emerge over time in individuals who have never smoked.

Statistical methods for secondary study end points will include the following: for comparisons of each study arm for parameters such as MGI assessment, plaque imaging, dental shade quantitation, tooth stains scores, and oral health–related quality of life questionnaires, the Shapiro-Wilk test of normality on calculated values (in case of normal distribution, a 2-sided independent *t* test and in case of nonnormal distribution: a 2-sided Mann-Whitney *U* test); for comparisons of each assessment time for parameters such as MGI assessment, plaque imaging, dental shade quantitation, tooth stains scores, and oral health–related quality of life questionnaires, the Shapiro-Wilk test of normality on calculated values (in case of normal distribution, a 2-sided independent *t* test and in case of nonnormal distribution: a 2-sided Mann-Whitney *U* test); accounting for missing, unused, and spurious data.

If only one value of the parameter MGI is missing after day 1, the last available observation will be carried forward. The analysis will be performed on the substituted data. For secondary parameters, no replacement of missing values will be applied.

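### The primary comparison is sized as a 1-sided 5% t test but analysed 2-sided with no stated alpha; at 2-sided 5%, 77 evaluable per group give 83.5% power, not 90%

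*Protocol article*

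**What the plan says.** Under Sample Size Calculation, the protocol article states: "The following hypotheses will be tested with a 1-sided independent" t test. The hypotheses are directional: "H0: µA≤µB versus H1: µA>µB". Table 5 is introduced as a 1-sided calculation with "a significance level of 5%, and a power of 90"%. From it the plan selects one cell, "a mean MGI change of 0.1 with an SD of 0.21 was chosen", and concludes that "a sample size of 77 patients per treatment group is required". That figure is raised to 92 for dropout. Arm B is then multiplied by four, to 368, because only about a quarter of it is expected to stop or cut smoking by at least 90%, and only that quarter is regarded as giving valid results.

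Under Statistical Analyses, the primary end point is checked for normality and then tested: "in case of normal distribution, a 2-sided independent" t test, otherwise a 2-sided Mann-Whitney U test. The Methods paragraph of the abstract agrees: "based on distribution, either a 2-sided" t test or Mann-Whitney U test. Neither place gives a significance level. The only 5% in the document belongs to the 1-sided calculation. The analysis section also mentions 95% confidence intervals, but lists them with the descriptive statistics.

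**The concern.** The sample size section does not present the 1-sided test as a planning device. It says that this is how the hypotheses will be tested. The article therefore states two different confirmatory tests for one primary end point.

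Two things are at stake. First, the decision rule is open: a result favouring arm B with a 2-sided p-value between 0.05 and 0.10 would succeed under the sample size section and, at 2-sided 5%, fail under the analysis section. Second, the quoted 90% power belongs to the 1-sided test. If the 2-sided test is run at 5%, the chance of missing the assumed effect is 16.5% rather than about 10% on the planned 77 per group.

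**Working it through.** **Inputs from the article.** Difference d = 0.10, SD = 0.21, significance level 5%, target power 90%, 77 per group, dropout 20%, 92 per group after dropout. **Assumption, not stated in the article:** the 2-sided test is run at 5%.

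**Formula.** For n per group, the two-sample t test has 2n − 2 degrees of freedom and noncentrality d / (SD × √(2/n)). Power is the probability that a noncentral t variable exceeds the critical value. For a 2-sided test the opposite tail is added, which is negligible here.

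**Step 1: reproduce the plan's figure.** For n = 77, the noncentrality is 0.10 / (0.21 × √(2/77)) = 2.955 with 152 degrees of freedom. The 1-sided 5% critical value is 1.655 and power is 90.3%. For n = 76, power is 89.9%. So 77 is the smallest n that reaches 90%, as stated. The same method reproduces all 15 entries of Table 5, so the table is 1-sided in its numbers as well as its label.

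**Step 2: same n, 2-sided 5%.** The noncentrality is unchanged and the critical value rises to 1.976. Power is 83.5%, so the miss rate is 100 − 83.5 = 16.5%. This change is due to sidedness alone.

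**Step 3: n for 90% power at 2-sided 5%.** For n = 93, power is 89.8%; for n = 94 it is 90.1%. So 94 evaluable per group are needed, against 77. The 0.10 row of Table 5 would become:

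| SD | 0.20 | 0.21 | 0.22 | 0.23 | 0.24 |
|---|---|---|---|---|---|
| Table 5, 1-sided 5% | 70 | 77 | 84 | 92 | 100 |
| 2-sided 5% | 86 | 94 | 103 | 113 | 123 |

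**Step 4: true 20% loss from 92.** 92 × 0.8 = 73.6, so 73 to 74 per group remain. The 92 matches 77 × 1.2 = 92.4, whereas keeping 77 after a 20% loss needs 77 / 0.8 = 96.25, that is 97. This is a separate shortfall.

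| n per group | 1-sided 5% | 2-sided 5% |
|---|---|---|
| 77 | 90.3% | 83.5% |
| 74 | 89.2% | 82.1% |
| 73 | 88.8% | 81.5% |

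**Step 5: sensitivity to the assumed alpha.** A 2-sided 10% test uses the same upper critical value as the 1-sided 5% test, so power at n = 77 stays at 90.3%.

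**Step 6: the Mann-Whitney branch.** With an assumed efficiency of 0.955 against the t test on normal data, 2-sided 5% power is about 82% at 77 per group and about 80% at 73.6.

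**The case against.** The strongest reply accepts the contradiction and disputes what may be inferred from it. Most of that reply stands.

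- *A reader might infer that the trial's true power is 82% to 84%.* The article does not support this as a plain fact. It gives no alpha for the 2-sided test, and 2-sided 10% would preserve 90.3%. The 5% reading is the natural one, since no other level appears and nothing suggests 10%, but it is an assumption. On either reading the text must be corrected.
- *A reader might attribute the whole fall to about 82% to sidedness.* Sidedness explains 90.3% to 83.5%. The rest comes from the dropout inflation, which lowers the 1-sided power too, to 88.8% to 89.2%. Moreover, last-observation-carried-forward applies when a single MGI value is missing, so someone who misses only the final visit stays in the analysis. The 73 to 74 is therefore a lower bound.
- *The analysis section does not restrict arm B to those who switched.* This is correct. With all of arm B analysed, about 74 against 294, 2-sided 5% power would be about 95% if the full 0.10 applied to everyone. It would be about 15% if non-switchers gained nothing, because the average effect would then be 0.25 × 0.10 = 0.025 (an assumption for illustration). The figures above are tied to the sizing basis and to no other population.
- *Baseline adjustment might be expected to recover most of the loss.* That depends on the correlation between baseline and 18-month MGI, which is not given. Assuming equal variances at the two times, 74 per group would have about 91% power at a correlation of 0.5, 88% at 0.7 and 86% at 0.8. No recovery can be promised.
- *The abstract's promise of "key insights into oral health benefits or risks associated with using C-F NA" might be read as an objective that a 1-sided test cannot serve.* It is a concluding remark; the stated objective concerns improvements, and the analysis section is already 2-sided. The argument has no practical effect.
- *The 2-sided analysis is the conservative choice, and power stays above 80% on the t test.* This is true if alpha is 5%, and it limits the harm. It does not make the stated 90% correct for that test.

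**Conclusion.** The contradiction is real and lies in the current text: one primary end point, a 1-sided test in the sample size section, a 2-sided test in the abstract and analysis section, and no alpha for the latter. An analysis plan that is not shown cannot remove it, because the article itself states both tests.

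At 2-sided 5%, the planned 77 evaluable per group have 83.5% power rather than 90%, and 94 would be needed. With 73 to 74 per group after a true 20% loss, power is 81.5% to 82.1%, part of which is the separate dropout shortfall.

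These results rest on four conditions: alpha of 5% 2-sided, a difference of 0.10 with SD 0.21, the t-test branch, and an evaluable arm B made up of the roughly 25% who stop or reduce smoking by at least 90%. The point should be corrected before analysis because it governs the primary inference. It does not show that the trial is unworkable or that its type I error is inflated under the 2-sided 5% test.

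**What to change.** 1. Keep the 2-sided test in the abstract and Statistical Analyses section, and state its alpha as 5%.
2. Rewrite the hypotheses under Sample Size Calculation as 2-sided, and recompute or relabel Table 5 to match.
3. Restate power as about 83.5% for 77 evaluable per group and about 82% for 73 to 74. Name the population: on the arm B side, those who stop or reduce smoking by at least 90%.
4. If a baseline-adjusted model is mentioned as a way to regain power, give the result as a range over an assumed correlation.

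The cost is wording and one restated power figure. Enrollment closed in June 2023, and no added participants are needed. The change should be dated and made before arm-level outcome data are examined.

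### The 20% dropout allowance is computed as 77 × 1.2 rather than 77/0.8, so 92 per group falls slightly short, and the trial is sized on 0.10 although the text calls 0.08 relevant

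*Protocol article*

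**What the plan says.** All of this stands in the Sample Size Calculation section of the protocol article.

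- From earlier mouth rinse studies, "a mean MGI change of 0.08 with an SD of 0.18 of the MGI seemed relevant". The section adds that larger changes were seen in those studies because an active treatment was given. It does not say how large.
- Since this trial gives no active treatment, an effect below those observed values is to be assumed. "Therefore, a mean MGI change of 0.1 with an SD of 0.21 was chosen".
- The test is stated as one-sided ("The following hypotheses will be tested with a 1-sided independent" *t* test), with "a significance level of 5%, and a power of 90"%. "Hence, a sample size of 77 patients per treatment group is required".
- With a dropout rate of 20%, described as applying to a 2-year observation phase, "a sample size of at least 92 per treatment group is required".
- About 25% of arm B are expected to stop smoking or cut down by at least 90%, and only they are counted as giving valid results. Arm B is therefore set at four times 92. "This results in a total sample size of 460 (92 in arm A+368 in arm B").

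Table 5 gives sample sizes for mean changes of 0.10, 0.15 and 0.20. It has no row for 0.08.

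**The concern.** Two steps in the justification need attention.

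First, the dropout step. An allowance for 20% loss should leave the required 77 after the loss. Taking 20% off 92 leaves 73.6, below the number required one sentence before. The shortfall is then multiplied by four for arm B and carried into the total.

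Second, the choice of effect. The only change the section quantifies from the earlier studies, and the one it calls relevant, is 0.08. The trial is sized on 0.10. A reader who takes 0.08 as the difference that matters will assume 90% power for it, and the section gives no figure for that case.

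At stake is how the result is read. If the primary comparison is not significant, it will be judged against a claimed 90% power, so that claim should match the numbers recruited and name the effect to which it applies.

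**Working it through.** **Inputs**, all from the Sample Size Calculation section: one-sided α = 0.05; power 0.90; δ = 0.10 with σ = 0.21 (chosen); δ = 0.08 with σ = 0.18 (called relevant); dropout 20%; arm B multiplier 4.

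**Method.** Two-sample *t* test with n per group. Power = P(T > t₀.₉₅), where T is noncentral *t* with 2n − 2 degrees of freedom and noncentrality λ = (δ/σ)·√(n/2).

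**1. Reproduce the plan's figure.** At δ/σ = 0.10/0.21 = 0.476, the smallest n with power of at least 0.90 is 77 (λ = 0.476 × √38.5 = 2.95; power 90.3%). All 15 cells of Table 5 reproduce by the same method, so the evaluable number is sound.

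**2. The dropout step.**

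- Multiplying up: 77 × 1.2 = 92.4. Rounded down, this is the stated 92.
- Dividing by the retained fraction: 77/(1 − 0.20) = 96.25, so 97.
- Left from 92 after 20% loss: 92 × 0.8 = 73.6.
- Largest dropout at which 92 still leaves 77: 1 − 77/92 = 16.3%.

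**3. Carry forward on the plan's own steps.**

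| | Stated | With 77/0.8 | Shortfall |
|---|---|---|---|
| Arm A | 92 | 97 | 5 |
| Arm B (× 4) | 368 | 388 | 20 |
| Total | 460 | 485 | 25 |

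Arm B gives the same result: 368 × 0.8 × 0.25 = 73.6 participants counted as valid.

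**4. One-sided power by scenario.**

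| Scenario | n per group | Power |
|---|---|---|
| 0.10 / 0.21 | 77 | 90.3% |
| 0.10 / 0.21 | 74 | 89.2% |
| 0.10 / 0.21 | 73 | 88.8% |
| 0.08 / 0.18 | 77 | 86.4% |
| 0.08 / 0.18 | 74 | 85.2% |

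For 90% power at 0.08/0.18, 88 evaluable per group are needed, which is 88/0.8 = 110 recruited per group before the arm B multiplier.

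**5. Which scenario is more favorable.** 0.10/0.21 = 0.476 and 0.08/0.18 = 0.444. The larger SD does not offset the larger effect. The chosen scenario is the easier one to detect on the standardized scale too.

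**The case against.** **The dropout rate is a 2-year rate and the trial lasts 18 months.** Scaled at constant hazard, 20% over 24 months becomes 1 − 0.8^0.75 = 15.4% at 18 months; pro rata it is 15%. Either is below 16.3%, and 92 would leave 77.8 or 78.2, enough for 77. This is the best defense of the number 92. However, the section does not say that it scaled the rate, and scaling does not produce 92 (77/0.846 = 91.0; 77/0.85 = 90.6), whereas 77 × 1.2 does. It stands as a possible repair that the authors would have to state.

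**A missing last visit need not remove a participant.** Under Statistical Analyses, if only one MGI value is missing after day 1, the last observation is carried forward. Someone who misses only the day 540 visit therefore stays in the analysis, and 73.6 is a lower bound at 20% dropout. This is true, but the sample size section does not use it and inflates for dropout in full.

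**The loss is about one point of power.** This is correct, and it limits the weight of the first part.

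**A reader might infer that the plan contradicts itself by presenting 0.10 as a reduction from 0.08.** The text does not support that. The effect is said to be below the values observed under active treatment, which are described as higher and are not quantified. If they exceed 0.10, the sentence is consistent. What stands is that the document gives no figure for them, so the claim cannot be checked, and that the trial is sized above the one change called relevant.

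**A reader might also pair 0.08 with SD 0.21 and report about 75% power, or add a two-sided test and go lower.** The section proposes no such scenario; its 0.08 comes with SD 0.18. The planned analysis is indeed two-sided ("in case of normal distribution, a 2-sided independent" *t* test), while the sizing is one-sided. That mismatch is a separate matter and should not enlarge this one.

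**Conclusion.** The stated 92 is wrong as an allowance for 20% dropout. It should be 97, with 388 in arm B and 485 in total; the plan is 25 participants, or about 5%, below what its own steps give. The practical effect is small: about 74 evaluable per group and about 89% one-sided power at 0.10/0.21, against 90.3% at 77.

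The choice of effect has the larger consequence. The 90% refers to a change of 0.10. For the 0.08 (SD 0.18) that the section calls relevant, one-sided power with 74 per group is about 85%. This is a gap in the justification and not a proven contradiction.

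These figures assume normal data, a one-sided 5% test, equal evaluable groups (on the plan's premise that only about a quarter of arm B counts), and the 20% rate applied unscaled, as the section applies it. Overall the point is minor to moderate. It does not put the design in doubt.

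**What to change.** Keep 460, since enrollment was completed in June 2023. In the Sample Size Calculation section, or in an erratum or the results paper:

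1. State that 92 per group leaves about 74 evaluable at 20% dropout, with about 89% one-sided power at 0.10/0.21. If the 2-year rate was meant to be scaled to 18 months, state the resulting rate of about 15% and show that 92 then suffices.
2. Report power at 0.08/0.18: about 85% one-sided with 74 per group, and 88 evaluable per group needed for 90%. A 0.08 row, with an SD 0.18 column, can be added to Table 5.
3. Give the observed mean changes from the mouth rinse studies that 0.10 is said to lie below, and explain why 0.10 was used in place of 0.08.

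The cost is a correction to the text and one table. No recruitment, endpoint or analysis changes. The stated power becomes slightly less favorable, unless the scaled dropout rate was what the authors intended.

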Finally, compliance with the research protocol is important because it would decrease or nullify the anticipated improvements in study end points if cigarettes were not fully or largely replaced with C-F NA. Participants will be reminded of the importance of adhering to their randomized product allocation and of abstaining from or substantially reducing the daily consumption of cigarettes (by at least 90% of their regular cigarette smoking at baseline) at every study visit. A significant feature of switching studies is close reporting of cigarette consumption and (or) C-F NA use; participants will record the consumption of cigarettes and use of C-F NA on each visit in their study diary. In addition, participants will be asked to return all empty, partly used, and unused consumables. Throughout the study, smoking and C-F NA use will be monitored via an app. The SMILE Tracker app is an integral component of the Smile study designed to monitor participants’ behaviors and lifestyle choices. Through daily prompts, the app assists in tracking cigarette consumption, use of combustion-free nicotine delivery systems, and regular oral hygiene practices such as brushing, flossing, and mouthwash use. In addition, it functions as a personal diary for participants to log any changes in their oral care routine. Moreover, the SMILE Tracker app features a system to monitor protocol adherence, identify deviations, and gather data on potential AEs and SAEs. It sends automated reminders to participants for their upcoming appointments and study restrictions and provides instructions to ensure adherence and accurate data collection during the study. Furthermore, it includes a step counter to encourage physical activity among users. Of note, noncompliance with the study items is an interesting outcome in itself (particularly in consideration of the wide selection of different products offered in the study). Although compliance with this study is not expected to be significantly different compared with other comparable studies, our power calculations are overestimated to account for a 75% noncompliance rate. The C-F NA population would therefore be overrepresented by recruiting4 times the number of participants in the C-F NA category (ie, for every participant randomized in the control population, 4 will be randomized in the C-F NA population).

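### The sample size, the 1:4 allocation and the 90% power rest on a switcher subgroup of arm B chosen after randomisation, so the 90% does not apply to the randomised comparison of arm A with arm B

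*Protocol article*

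**What the plan says.** **Sample size.** The Sample Size Calculation states "a mean MGI change of 0.1 with an SD of 0.21 was chosen". With a one-sided t test at "a significance level of 5%, and a power of 90"%, it arrives at 77 per group, raised to 92 for 20% dropout. It then expects about 25% of arm B to abstain or reduce smoking by at least 90%, "and only these participants deliver valid results. Therefore, 4 times more participants should be recruited in the C-F NA group". Arm B becomes 4 × 92 = 368 and the total 460.

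**Allocation.** Study Design gives the same expected 25% as the reason for randomising 1:4. The Discussion (Overview) repeats the logic: "our power calculations are overestimated to account for a 75% noncompliance rate".

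**Primary contrast.** The abstract's Methods give the end point as the "change in the Modified Gingival Index (MGI) score from baseline between the control arm (arm A) and the intervention arm (arm B") at 18 months. Primary End Points describes a comparison "among participants who continue to smoke tobacco cigarettes (arm A) and participants who switch to C-F NA (arm B").

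**Analysis.** Statistical Analyses specifies a two-sided t test or Mann-Whitney U test, plus a linear mixed model with centre and arm-by-centre as random factors. It does not say who is included.

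**The concern.** The sample-size argument treats the 75% of arm B who are not expected to switch as uninformative and recruits extra participants to replace them. That restores the number of switchers but not their comparability with arm A. Arm A still contains the smokers who would have switched had they been offered products; arm B, on this reasoning, is reduced to those who did. The Discussion itself says that oral hygiene, diet and alcohol affect gum outcomes, and people who manage a 90% reduction may differ on these. A difference between switchers and arm A could then appear without any product effect.

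If all randomised participants are compared instead, as the abstract's wording implies, the effect is diluted by the non-switchers and the 90% power has not been shown for that comparison. At stake is whether the headline result is a randomised comparison and whether the trial has the power that a reader will credit it with.

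**Working it through.** **Inputs from the protocol.** Difference 0.10, SD 0.21, significance level 5%, power 90%, dropout 20%, switchers 25% of arm B (Sample Size Calculation). The sample size uses a one-sided test: "The following hypotheses will be tested with a 1-sided independent" t test. The planned analysis is two-sided: "in case of normal distribution, a 2-sided independent" t test (Statistical Analyses). The effect in non-switchers is not given. The Discussion says only that failure to replace cigarettes would reduce or cancel the improvement, so a range is used below.

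**1. Reproducing the plan's figure.** For a two-sample t test, the noncentrality is δ / [SD × √(1/n_A + 1/n_B)]. With 77 v 77, this is 0.10 / (0.21 × √(2/77)) = 0.10 / 0.0338 = 2.95. One-sided power is 90.3%, so 77 is confirmed, and all 15 cells of Table 5 reproduce exactly. The 92 is 77 × 1.2 = 92.4, and 4 × 92 + 92 = 460. The 90% is thus the power for 77 evaluable arm A participants against 77 evaluable switchers.

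**2. The same contrast under the planned two-sided test.** At 77 v 77, power is 83.5%. After 20% loss from 92 (92 × 0.8 = 73.6, about 74), 74 v 74 gives 82% two-sided and 89% one-sided.

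**3. The whole-arm comparison.** Completers are about 74 in arm A and 368 × 0.8 = 294 in arm B. The standard error is 0.21 × √(1/74 + 1/294) = 0.0273. The expected difference is 0.25 × 0.10 + 0.75 × f, where f is the assumed effect in non-switchers.

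| Assumed f | Expected difference | Power, two-sided 5% | Power, one-sided 5% |
|---|---|---|---|
| 0 | 0.025 | 15% | 23% |
| 0.02 | 0.040 | 31% | 43% |
| 0.05 | 0.0625 | 63% | 74% |
| 0.075 | 0.081 | 84% | 91% |

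With f = 0 and no dropout (92 v 368), the figures are 17% and 27%. Allowing for the extra spread from mixing switchers and non-switchers in arm B (SD 0.214) changes almost nothing: 14.7% and 23.2%. All rows assume that nobody in arm A quits or switches; quitting in arm A would lower the power.

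**4. Illustration of selection, with no product effect.** Suppose the propensity to switch has correlation r with MGI change, in the direction favouring switchers, and the top 25% switch. The switchers' mean then shifts by r × 0.21 × φ(z₀.₇₅)/0.25 = r × 0.21 × 0.318/0.25 = r × 0.267. For an unadjusted two-sided test at 74 v 74:

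| Assumed r | Shift | False-positive rate |
|---|---|---|
| 0.05 | 0.013 | about 7% |
| 0.1 | 0.027 | 12% |
| 0.2 | 0.053 | 34% |
| 0.3 | 0.080 | 63% |

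The correlations are assumptions. No figure in the protocol supports any one of them.

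**The case against.** A reader might infer that the primary analysis will drop the non-switchers. The protocol does not say so. The restriction appears in the sample-size rationale, while Statistical Analyses names no population and its mixed model is built on study arms. Populations are commonly left to an analysis plan, which is not shown. Primary End Points is also ambiguous: its wording contrasts continuing with switching, but it labels the groups by arm and gives no reduction threshold. No passage removes quitters from arm A. All of this stands and limits the point to the basis of the sample size and power, together with an unresolved primary contrast.

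A second tempting reading is that the protocol claims 90% power for the whole arms and really has 15–23%. It makes no such claim, and 15–23% requires exactly zero benefit in the other 75% of arm B, which is the extreme of the Discussion's own wording. Hence the range. Even so, about 0.075 in non-switchers, three quarters of the full effect, is needed to reach roughly 90%, and then only one-sided. That sits badly with the premise that only switchers are informative.

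Third, all randomised smokers must be willing to switch and must have declined cessation programmes. Regression and analysis of covariance adjusting for age, gender and oral hygiene frequency are also planned. These may reduce selection bias, but they do not restore randomisation. The false-positive rates describe an unadjusted test and are illustrations, not predictions.

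**Conclusion.** The concern holds in this form. The sample size, the 1:4 ratio and the 90% power are justified on a contrast that randomisation does not protect, whereas the abstract states the primary contrast by arm and nothing in the article reconciles the two. An analysis plan could name the population, but it could not make this sample-size argument apply to the randomised comparison.

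The 90% does not carry over to that comparison. On the plan's own 0.10, SD 0.21, 25% and 20%, power runs from 15–23% with no benefit in non-switchers to 84–91% if they gain 0.075, assuming no quitting or switching in arm A. The switcher contrast itself does not have 90% power under the planned two-sided test. The direction and size of any selection bias cannot be determined from the protocol.

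**What to change.** 1. Name one primary analysis: all randomised arm A versus all randomised arm B, change in MGI at month 18. State its power with the range above and the assumption behind each value. Align the abstract, Primary End Points and Sample Size Calculation with it.
2. Delete the statement that only those who abstain or substantially reduce give valid results.
3. Report switchers versus arm A as a supportive, baseline-adjusted comparison, labelled non-randomised. Replace its 90% with the power for the two-sided test: about 82% at 74 v 74, or 83.5% at 77 v 77.
4. As a secondary analysis, estimate the complier-average effect with randomisation as the instrument. State that it will be inflated if partial reducers below the 90% cut-off also benefit, because assignment must then have no effect on them for the estimate to be valid.

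Enrolment is complete, so the cost is wording and one additional analysis. The price is a less favourable stated power for the randomised comparison and a wider interval for the effect in switchers.
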